## Abstract

**Background:**

Postoperative pulmonary complications (POPC) are common after general anaesthesia and are a major cause of increased morbidity and mortality in surgical patients. However, prevention and treatment methods for POPC that are considered effective tie up human and technical resources. Therefore, the planned research project aims to create a prediction model that enables the reliable identification of high-risk patients immediately after surgery based on a tailored machine learning algorithm.

**Methods:**

This clinical cohort study will follow the TRIPOD statement for multivariable prediction model development. Development of the prognostic model will require 512 patients undergoing elective surgery under general anaesthesia. Besides the collection of perioperative routine data, standardised lung sonography will be performed postoperatively in the recovery room on each patient. During the postoperative course, patients will be examined in a structured manner on postoperative days 1,3 and 7 to detect POPC. The endpoints determined in this way, together with the clinical and imaging data collected, are then used to train a machine learning model based on neural networks and ensemble methods to predict POPC in the early postoperative phase.

**Discussion:**

In the perioperative setting, detecting POPC before they become clinically manifest is desirable. This would ensure optimal patient care and resource allocation and help initiate adequate patient treatment after being transferred from the recovery room to the ward. A reliable prediction algorithm based on machine learning holds great potential to improve postoperative outcomes.

**Trial registration:**

ClinicalTrials.gov ID: NCT05789953 (29th of March 2023)

## Introduction

The incidence of postoperative pulmonary complications (POPC) varies between 9–40%, depending on the surgical procedure and the definition used [1]. Therefore, the introduction of a standardised definition of the outcome “postoperative pulmonary complications”, developed by the Standardised Endpoints for Perioperative Medicine (StEP) collaboration in 2018, represents a prerequisite for future studies in this field [1]. Even supposedly minor complications have the potential to significantly increase the length of hospital stay [2]. Various preoperative risk factors are known but usually cannot be modified. As POPC are the main cause of postoperative morbidity and mortality and the reduction of perioperative mortality is dependent on early recognition and treatment [3], accurate prediction is of paramount interest. There are only a few clinical scoring systems [4]; the currently best-evaluated preoperative score for predicting postoperative pulmonary complications (ARISCAT: Assess Respiratory Risk in Surgical Patients in Catalonia, Table 1) has sufficient sensitivity but lacks specificity [5]. A first retrospective study using machine-learning (ML) methods for determining risk for pneumonia and pulmonary embolism using pre- and intraoperative routine data has shown good accuracy [6]. However, the study shows high specificity but low sensitivity, which could result in overtreatment in clinical practice. In our study, we aim to create a high precision decision-supporting tool for perioperative physicians to identify high-risk patients at an early stage.

**Table 1 pone.0329076.t001:** ARISCAT score.

Score parameters	components	Risk score
Age	≤ 50 years	0
	51-80 years	3
	> 80 years	16
Preoperative oxygen saturation	≥ 96%	0
	91-95%	8
	≤ 90%	24
Respiratory infection in past 1 month	No	0
	Yes	17
Preoperative hemoglobin ≤ 10 mg/dl	No	0
	Yes	11
Incision	Peripheral incision	0
	Upper abdominal incision	15
	Intrathoracic incision	24
Surgery duration	<2h	0
	2-3h	16
	> 3h	23
Emergency procedure	No	0
	Yes	8
**ARISCAT Score**	**Risk**	**Total**
	Low Risk	< 26
	Intermediate Risk	26-44
	High Risk	≥ 45

The table was adapted from [5]; The article was published under the Creative Commons Attribution (CC BY 4.0) license (https://creativecommons.org/licenses/by/4.0/). ARISCAT = Assess Respiratory Risk in Surgical Patients in Catalonia.

However, ML algorithms based only on routine clinical data depend highly on data quality and comprehensiveness. Algorithms based on standardised imaging data are easier to transfer to other facilities and implement in routine clinical practice. Therefore, combining image analysis might be beneficial, especially as sonography is becoming increasingly important as a non-invasive examination method that can be performed at the bedside. Various sonographic scores and models have been developed to predict pulmonary complications [7]. Image processing methods and machine learning, particularly deep learning, are also increasingly used in ultrasound diagnostics [8,9]. Augmented algorithms using pre- and intraoperative clinical information in addition to ultrasound imaging data may provide better predictive accuracy than the respective individual methods. However, to our knowledge, combining routine clinical data and ultrasound imaging data to develop a predictive machine-learning algorithm has not yet been tested. In addition, prospective clinical evaluation of machine-learning algorithm-based prediction models, which is planned herein, lacks to date.

Measures for preventing POPC, such as postoperative non-invasive ventilation and physiotherapy, are known and considered effective [10,11] but are probably not consistently applied in clinical routine due to the increased demand, especially for human resources.

This study aims to combine pre- and intraoperative data with lung ultrasound imaging in the recovery room to develop an ML-based risk score for POPC. A precise score that reliably identifies patients at risk in the early postoperative phase and simultaneously avoids overtreatment can ensure adequate personalised treatment of postoperative patients.

## Materials and Methods

### Trial registration

Name of the registry: ClinicalTrials.gov

Registration ID: NCT05789953

Approval date: 29/03/2023

### Ethics approval

Name: Ethics committee University of Ulm

Approval Number: 369/22

Approval date: 22^/^12/2022

Head of committee: [name]. [name], [name]

Mail: [contact]

Homepage: https://www.uni-ulm.de/einrichtungen/ethikkommission-der-universitaet-ulm/

Written informed consent to participate will be obtained from all participants.

### Objectives

The main hypothesis of the PEPPERMINT study is that a patient’s risk of POPC can be reliably predicted using a machine-learning algorithm and that the predictive accuracy of the algorithm outperforms common clinical scoring systems.

The primary objective is to develop a machine-learning algorithm based on immediately postoperatively obtained lung ultrasound imaging data of adult patients undergoing surgery in general anaesthesia to predict the risk of postoperative pulmonary complications. This model is intended to provide better predictive ability than the currently best-established clinical score, the ARISCAT [5] or a machine learning model solely based on clinical routine data.

The secondary objective is to investigate whether improving model performance by adding clinical routine parameters to the imaging data is possible.

Furthermore, the optimal risk threshold for an intervention will be determined in case of a clinical application of the model.

Further objectives include identifying patient-specific risk factors for POPC through analysis of the collected routine clinical data and modification of the models created to predict the secondary endpoints of hospital length of stay, in-hospital mortality and postoperative quality of recovery.

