### Model training and evaluation

The primary model development will be based on a dataset of 512 patients. Within this cohort, we will implement stratified k-fold cross-validation (typically 5- or 10-fold, depending on the final class distribution) where possible to assess model robustness and mitigate overfitting. Image-based deep learning models require extensive computational resources, therefore, cross-validation will be applied more selectively. We will therefore use a fixed training/validation/test split for imaging data, ensuring non-overlapping patient groups. Early model experiments will be conducted using internal validation on the training data with hold-out validation to optimize architecture and hyperparameters. Final model evaluation will be performed on an independent hold-out test set.

This hold-out test set will be compiled prospectively during the course of the study after model development, using newly enrolled patients not included in the training dataset. This temporal separation will ensure unbiased performance evaluation of the final model.

Model performance will be evaluated on the independent hold-out test set using several complementary performance metrics. These will include the area under the receiver operating characteristic curve (AUROC), the area under the precision-recall curve (AUPRC), overall accuracy, sensitivity, specificity, F1-score, as well as positive and negative predictive values. Calibration will be assessed using appropriate measures, such as the Brier score, Hosmer-Lemeshaw-Test and calibration curves. Clinical decision-making utility can additionally be evaluated using decision curve analysis (DCA).

Importantly, our models are designed to output individualized risk probabilities, not dichotomous predictions. As such, the selection of a cut-off point for potential clinical decision-making will be a post-modelling step, and risk thresholds for high-risk patient classification will not be predefined. Instead, various thresholding strategies will be explored post hoc, including Youden’s index (for balanced sensitivity and specificity), cut-offs optimized for specific clinical priorities (e.g., maximizing sensitivity), and thresholds guided by DCA.

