### Addressing overfitting and class imbalance

Overfitting will be addressed through the implementation of several regularization techniques commonly used in deep learning. These include dropout layers within the network architecture, L2 weight regularization to penalize large weights, and data augmentation techniques applied to ultrasound images (e.g., rotation, flipping, and zooming). Model complexity will also be restricted as needed.

To better estimate the prevalence and clinical relevance of POPC, we conducted a preliminary single-center observational study involving 259 patients undergoing surgery under general anesthesia. The cohort included 106 female patients (41%) and 62 current smokers (24%) with a median age of 66 years. Overall, 111 patients (43%) experienced at least one POPC, indicating that POPC is a relatively frequent complication in the targeted patient population [25].

Based on this preliminary observational data, only moderate class imbalance is to be expected. Nevertheless, additional strategies will be employed to ensure balanced learning. These include maintaining class ratios across cross-validation folds, monitoring class-wise performance metrics, and using class weighting techniques if imbalances are observed in specific subgroups.

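### The protocol promises an optimal intervention threshold but states no trade-off that would define optimal, and leaves the choice to post hoc exploration of data-derived cut-offs

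*Protocol article*

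**What the plan says.** The Objectives section of the protocol article lists, after the primary and secondary objectives: "Furthermore, the optimal risk threshold for an intervention will be determined in case of a clinical application of the model".

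The section Model training and evaluation describes how. The models output risks, the cut-off is chosen after modelling, and "risk thresholds for high-risk patient classification will not be predefined". In place of a fixed value, the article offers an open list of options: "various thresholding strategies will be explored post hoc, including Youden’s index (for balanced sensitivity and specificity"), together with "cut-offs optimized for specific clinical priorities (e.g., maximizing sensitivity), and thresholds guided by DCA". DCA is also mentioned as an optional evaluation: "Clinical decision-making utility can additionally be evaluated using decision curve analysis (DCA").

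Four other statements bear on the point:
- The section on overfitting and class imbalance reports a preliminary cohort of 259 patients: "Overall, 111 patients (43%) experienced at least one POPC".
- Recruitement and informed consent, and Sample size, both plan roughly equal numbers in the three ARISCAT risk groups.
- Oversight and monitoring says that the study includes no intervention.
- The end of the Introduction sets two aims for the score: to find patients at risk and to avoid overtreatment.

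**The concern.** A threshold for intervening is optimal only relative to a weight: how many patients without POPC one would treat unnecessarily in order to treat one patient who would develop it. The article gives no such weight, no range of threshold probabilities, no minimum sensitivity or specificity, and no rule for choosing among strategies that will generally disagree. Nobody is treated in this study, so neither the benefit of treating a true positive nor the harm of treating a false positive is observed. The data cannot supply the missing input.

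Without it, a number reported as optimal would rest on a weight that nobody chose. The Strengths section describes a later study in which patients classified as high-risk by the model receive a treatment programme. A cut-off published as the optimal intervention threshold would be a natural candidate for that study, although the article does not say that it would be carried over.

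**Working it through.** **Inputs.** Event rate 111 of 259 (section on overfitting and class imbalance); published range of POPC incidence (Introduction: "The incidence of postoperative pulmonary complications (POPC) varies between 9–40"%); AUROC 0.83 for ARISCAT and 0.93 as the target (Sample size). Assumption made here: an equal-variance binormal score whose predicted risks are calibrated.

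**Plan's own figure.** 111/259 = 42.9%, which rounds to the stated 43%.

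**1. Youden's index.** Sensitivity + specificity − 1 is greatest where the likelihood ratio is 1. There the post-test odds equal the pre-test odds, so for a calibrated model the predicted risk at the cut equals the event rate p. On a grid, event rates of 9%, 20% and 43% gave cuts of 0.09, 0.20 and 0.43 at both AUROC values.

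Used as an intervention rule, a risk cut of p implies accepting (1−p)/p unnecessary treatments per necessary one:
- p = 0.09: 0.91/0.09 = 10.1
- p = 0.20: 0.80/0.20 = 4.0
- p = 0.43: 0.57/0.43 = 1.3

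So the implied trade-off follows from the mix of patients enrolled. Balancing by ARISCAT group partly sets that mix.

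The identity holds on average and under calibration. In 1,000 simulated data sets with p = 0.43 and AUROC 0.93, the Youden cut had a 95% range of 0.29 to 0.59 at n = 512 and 0.22 to 0.71 at n = 100. Miscalibration moves it as well: shifting the intercept by +0.5 on the logit scale gave a median of 0.56.

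**2. Maximising sensitivity.** With no constraint, the cut goes to 0 and everyone is flagged. Taking instead the highest cut that keeps 100% sensitivity in the sample, a median of 85% of patients are flagged at n = 512 and AUROC 0.93, and 95% at AUROC 0.83. A sensitivity target needs a stated limit on false positives before it says anything about overtreatment.

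**3. DCA.** Net benefit at threshold probability t is

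NB(t) = p × sensitivity − (1 − p) × (1 − specificity) × t/(1 − t).

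The factor t/(1 − t) is the trade-off, and it is an input. For p = 0.43 and AUROC 0.93:

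| t | sensitivity | 1 − specificity | t/(1−t) | NB |
|---|---|---|---|---|
| 0.01 | 0.999 | 0.847 | 0.010 | 0.425 |
| 0.10 | 0.975 | 0.450 | 0.111 | 0.391 |
| 0.30 | 0.906 | 0.220 | 0.429 | 0.336 |
| 0.43 | 0.852 | 0.148 | 0.754 | 0.302 |

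Worked line for t = 0.30: 0.43 × 0.906 − 0.57 × 0.220 × 0.429 = 0.390 − 0.054 = 0.336.

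Net benefit falls as t rises, so the height of the curve does not identify a best threshold. Choosing t where the gain over treat-all and treat-none is largest returns the event rate again.

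**4. With the trade-off fixed first.** If t is set beforehand, the cut that maximises net benefit for a calibrated model is t itself: inputs of 0.10, 0.20 and 0.30 gave cuts of 0.10, 0.20 and 0.30 at every event rate and AUROC tried. DCA then does its proper job. At p = 0.43, the gain over the better of treat-all and treat-none exceeds 0.01 for t from about 0.06 to 0.995 at AUROC 0.93, and from about 0.12 to 0.94 at AUROC 0.83. These values illustrate the method and are not proposed thresholds.

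**The case against.** The strongest reply is that the text is more open than a critic may allow.

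- A reader might infer that the named strategies cannot yield a threshold at all, or can only return the event rate or treat-all. The documents do not support that. The list of strategies is not closed. Maximising sensitivity is one example within a wider class of cut-offs set by clinical priorities, which could include a constrained target. The article speaks of thresholds guided by DCA and never says that the threshold will be placed where net benefit peaks. DCA combined with a stated trade-off can support a choice. All of this stands.
- The Youden identity needs calibration and is blurred by sampling. In the model used here, the Youden cut also sits at the same score, with the same sensitivity and specificity, at every event rate; only the risk attached to it changes. That is correct, and it limits the claim to the weight the cut implies. It does not make that weight a chosen one.
- The objective is conditional on clinical application, and no primary comparison and no patient in this study depends on it. That stands and limits the severity.
- The statistical analysis plan (S3 File) is not shown and may define the rule. This helps only in part: the article itself commits to having no predefined threshold and to post hoc exploration, alongside an objective that promises an optimum.
- A reader might also take the Introduction's remark on an earlier machine-learning study, "However, the study shows high specificity but low sensitivity, which could result in overtreatment in clinical practice", as proof that the trade-off was never considered. It is not proof. Low sensitivity with high specificity means missed cases rather than overtreatment, so the sentence reverses the error types. But it is background on a cited study, and the Introduction elsewhere names both aims correctly.

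**Conclusion.** The point holds as a gap between objective and method. The article promises an optimal threshold for intervening, declines to predefine one, and states no trade-off that would make any cut-off optimal. This non-interventional study cannot estimate that trade-off.

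A Youden cut should not be read as an intervention threshold. Under calibration it averages the sample event rate, about 0.43 on the preliminary figure, with a simulated 95% range of 0.29 to 0.59 at n = 512 and AUROC 0.93. The enrolled rate may differ from 43%, because the article gives no expected rate under ARISCAT-balanced recruitment. DCA compares models at a threshold probability supplied to it.

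The numbers rest on the equal-variance binormal model. The argument that DCA needs its threshold as an input does not. This should be corrected before outcomes are analysed; it does not affect the primary comparison of discrimination.

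**What to change.** 1. Before outcomes are analysed, have the study clinicians state a range of acceptable ratios of unnecessary to necessary treatments. Convert each ratio r to a threshold probability t = 1/(1 + r). No value is proposed here.
2. Within that range, use DCA to compare the three models, ARISCAT, treat-all and treat-none. ARISCAT needs mapping to a risk, for example by a logistic fit in the training data, because Table 1 gives points and risk groups but no probabilities.
3. Report Youden's index and other data-derived cut-offs as descriptive only.
4. Reword the objective to net benefit over a pre-stated threshold range. If the statistical analysis plan already contains such a range, refer to it in the article.
5. Separately, correct the reversed error types in the Introduction.

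The cost is one consensus step and some wording; no sample size, visit or measurement changes. The downside is that the paper can no longer claim a data-derived optimal cut-off.

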### Trial design

The PEPPERMINT study is a prospective, single-center clinical cohort study designed to develop and evaluate a risk prediction model for POPC. The study follows the TRIPOD (Transparent Reporting of a Multivariable Prediction Model for Individual Prognosis or Diagnosis) guidelines for multivariable model development and validation [12].

A total of 512 patients will be enrolled based on sample size calculation. For each patient, both clinical data and lung ultrasound images will be prospectively collected. The primary endpoint is the occurrence of any postoperative pulmonary complication, as defined by standardised criteria.

### Three predictive models will be developed

First, a model based on deep learning using lung ultrasound images, second, a model based solely on clinical variables using common frameworks like automated machine learning (AutoML), and finally, a combined model integrating both clinical and imaging features.

The dataset will be split using stratified, patient-wise sampling into non-overlapping training and hold-out test sets. Internal model performance will be assessed using k-fold cross-validation within the training set, and final evaluation will be conducted on the independent test set. Full details of the modelling and validation procedures are provided in the statistical methods.

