### Adverse events and harms

Patients will undergo routine perioperative care as per standard during this trial; responsible for patient care will be the attending physicians and departments. Additionally, patients will receive (1) a lung ultrasound, considered non-invasive and without side effects, and (2) a clinical examination and interview at up to three time points postoperatively. All other procedures are part of general anaesthesia or usual perioperative management and are completed even without study participation. Therefore, we do not expect any complications or harm from trial participation.

Nevertheless, patients can report adverse events or other unintended effects of the trial to the study hotline or email address. The trial steering committee will process the reports.

Due to the relatively small size of the data set, the prediction model will be developed using the whole dataset. Cross-validation will be used to evaluate the performance of the model. Furthermore, validation is planned on a temporally independent data set obtained during the period of model training. Therefore, the study will be classified as Type 1b according to the TRIPOD Statement [12].

Error analysis will be carried out with the help of a confusion matrix after threshold determination. The cases of incorrect predictions will be analyzed in more detail, in particular, to determine whether certain characteristics correlate with the errors. External validation will take place in future studies.

In the current study, we are not focusing on the identification of possible confounders for model performance. This will be done in a follow-up study, investigating the impact of possible confounders such as different raters, imaging devices, bad image quality, resolutions, etc., in a possibly multi-centric study.

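### The protocol article contradicts itself on which patients supply the final performance estimate: a part split off from the dataset, newly enrolled patients, or the whole dataset by cross-validation

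*Protocol article*

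**What the plan says.** All references are to the protocol article.

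- **Three predictive models will be developed.** "The dataset will be split using stratified, patient-wise sampling into non-overlapping training and hold-out test sets". Cross-validation runs inside the training part, and "final evaluation will be conducted on the independent test set". The section closes with a deferral: "Full details of the modelling and validation procedures are provided in the statistical methods".
- **Model training and evaluation** (part of the statistical methods). "The primary model development will be based on a dataset of 512 patients". *Trial design* gives 512 as the total to be enrolled. Cross-validation is used where possible, but for imaging: "We will therefore use a fixed training/validation/test split for imaging data, ensuring non-overlapping patient groups". Then: "This hold-out test set will be compiled prospectively during the course of the study after model development, using newly enrolled patients". The performance metrics are attached to that hold-out set.
- **Overview of modelling approaches.** The final architecture of the combined model is chosen by its performance in a hold-out test dataset. Which one is not said.
- **Adverse events and harms** (where a validation paragraph has been placed). Because the data set is small, "the prediction model will be developed using the whole dataset". Cross-validation evaluates performance. A temporally independent set is added, gathered while the model is being trained. From this the article concludes that "the study will be classified as Type 1b according to the TRIPOD Statement".

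**The concern.** The main hypothesis is comparative: the algorithm should predict better than common clinical scores, and *Objectives* names ARISCAT and a clinical-data-only model as comparators. The result therefore depends on which patients the AUROCs come from. The sections give different answers, and an analyst could not follow all of them.

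Three consequences follow:

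1. If development uses the whole dataset, a test set split from that dataset has been trained on, and its AUROC is no longer an independent estimate.
2. If the hold-out set that selects the combined architecture is also the final test set, the selected model's performance is biased upward.
3. The number of patients evaluated, and so the precision of the comparison with ARISCAT, differs greatly between the readings.

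**Working it through.** **Step 1. The statements side by side**

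| Section | Developed on | Final performance from |
|---|---|---|
| Three predictive models will be developed | Training part of the dataset | Hold-out part split from the same dataset |
| Model training and evaluation | 512 patients; imaging also has a fixed training/validation/test split | Patients enrolled after development |
| Adverse events and harms | Whole dataset | Cross-validation, plus a temporal set gathered during training |

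- Rows 2 and 3 largely fit together: develop on everyone, cross-validate, then test on later patients. They still differ on when the temporal set is gathered, and row 3 names cross-validation as the evaluation.
- Row 1 fits neither. Against row 3, patients cannot be both reserved from development and included in it. Against row 2, the hold-out set cannot be both sampled from the dataset and made up of new patients.
- The imaging test split in row 2 is a further test set whose relation to the later-enrolled set is not stated.

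**Step 2. The plan's own figure**

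*Sample size* gives 512 for AUROC 0.93 against 0.83 (significance level 0.05, power 80%, Hanley and McNeil). It does not state the event rate or the correlation r between the two AUROCs, so 512 can be neither confirmed nor refuted. With the pilot's 43% (111/259, *Addressing overfitting and class imbalance*), a two-sided test in the same patients and the variance under the alternative, 80% power needs about 210 patients at r = 0 or 114 at r = 0.5.

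**Step 3. Precision under each reading**

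Inputs: event rate 43% (pilot); AUROC A = 0.83 (*Sample size*); total 512. Assumed, because the article states no split: test fractions of 10%, 20% and 30%, that is 51, 102 and 154 patients.

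Hanley-McNeil variance, with n1 events and n0 non-events:

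Var(A) = [A(1 − A) + (n1 − 1)(U − A²) + (n0 − 1)(V − A²)] / (n1·n0), where U = A/(2 − A) and V = 2A²/(1 + A).

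For A = 0.83: A² = 0.6889, U = 0.83/1.17 = 0.7094, V = 1.3778/1.83 = 0.7529.

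For n = 102: n1 = 43.86, n0 = 58.14.
Var = [0.1411 + 42.86 × 0.0205 + 57.14 × 0.0640] / (43.86 × 58.14) ≈ 4.677/2550 = 0.001834, so SE = 0.043.

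The same formula gives the other rows. Power is for 0.93 against 0.83, two-sided 0.05, with r assumed from 0 to 0.5: power = Φ(0.10/SE_diff − 1.96), where SE_diff² = SE₁² + SE₂² − 2r·SE₁·SE₂.

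| Patients evaluated | SE at 0.83 | SE at 0.93 | Power |
|---|---|---|---|
| 51 (10%, assumed) | 0.061 | 0.040 | 28–46% |
| 102 (20%, assumed) | 0.043 | 0.028 | 50–76% |
| 154 (30%, assumed) | 0.035 | 0.023 | 67–90% |
| 512 (all) | 0.019 | 0.013 | at least 99% |

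The last row treats cross-validated predictions approximately as one sample of 512.

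For a later-enrolled test set, 80% power at 43% events needs the 114 to 210 patients of step 2. If these came from within the 512, between 512 − 210 = 302 and 512 − 114 = 398 would remain for development.

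**The case against.** The best defence is that the article does identify a final test set. The overview defers to the statistical methods, and those place final evaluation on newly enrolled patients and attach the metrics to them. Only one sentence, in a misplaced paragraph, names cross-validation as the evaluation, and temporal validation follows at once. Split fractions and test-set size may also sit in the separate analysis plan, which is not shown.

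Much of this stands. It is why these are not three mutually exclusive designs, and why the missing split fraction is not itself a fault. It does not remove the conflict. The section deferred to describes a different hold-out set from the one it should detail, keeps a separate imaging test split, and does not say whether the new patients are inside the 512. An unseen plan cannot make these published statements agree.

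A reader might infer more than the text supports:

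- **That Type 1b is the wrong TRIPOD label.** The article does not define the types, so this cannot be judged here. It can only be said that the label is derived from the whole-dataset account and must be rechecked once the design is settled.
- **That imaging and clinical models will be compared on internal estimates from different patients.** Their internal procedures do differ, for a stated computing reason, but no section plans that comparison.
- **That the most favourable of several results will be chosen.** Nothing says so; the ambiguity only leaves room for it.
- **That the overview's split is simple random.** It is described as stratified and patient-wise.

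**Conclusion.** The contradiction is real and should be resolved before analysis. The overview's split-off hold-out set is incompatible with developing on the whole dataset and with a hold-out set of new patients. The other two accounts can largely be combined, apart from the timing of the temporal set and the role of cross-validation. Choosing the combined architecture on an unnamed hold-out set adds a risk of optimism, conditional on that set being the final one.

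The finding rests on the text. The arithmetic shows only the consequence: at 43% events and AUROC 0.83, the SE is about 0.035 to 0.061 for assumed splits of 30% to 10%, against about 0.019 with all 512 evaluated. These figures depend on the pilot event rate, the assumed fractions and the one-sample approximation for cross-validation; the power ranges also depend on the assumed r.

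**What to change.** State one design, in the same terms, in *Three predictive models will be developed*, *Overview of modelling approaches*, *Model training and evaluation*, and the validation paragraph now under *Adverse events and harms*:

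1. Name one final test set, either split off and excluded from all development, or temporally later. Say whether it lies inside or beyond the 512.
2. Make every model, fusion and architecture choice within the training data only.
3. Score the imaging, clinical and combined models and ARISCAT on the same test patients, with a paired comparison.
4. Label cross-validation results, and any imaging split inside the training data, as internal only.
5. Recheck the TRIPOD type against the chosen design.

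The cost is rewording and some computing. It is not wording alone if the test set comes from within the 512: the development set then falls below the 512 now stated, and that figure must be restated. If the test set lies beyond the 512, more patients are needed. *Trial status* reports 150 patients included, so the choice can be fixed while most of the planned data are still to come.
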